## Methods

### Design

The current study will be a randomized controlled clinical trial, wherein a dismantling design will be used. The dismantling design consisted of analyzing the components of a treatment package by removing one component of therapy in one of the comparison groups [23]. Specifically, three groups will be compared: (a) a cognitive-behavioral intervention via conference call (CBC) with cognitive and behavioral techniques; (b) a behavioral activation intervention via conference call (BAC) with only behavioral techniques aimed at activating behavior; and (c) a control group (CG) in which caregivers receive usual care.

The phases of the study are shown in Fig. 1. There will be six measurement points in the three groups (i.e., pre-treatment, post-treatment and 1-, 3-, 6- and 12-month follow-ups). The first is baseline (pretreatment). Once the caregivers who meet the eligibility criteria are selected and we administer the interventions, we will conduct a post-treatment evaluation and four subsequent follow-ups at 1, 3, 6, and 12 months. To minimize the loss of subjects, we followed the strategies recommended by Grady and colleagues [24] such as excluding those participants likely to drop out; treat participants with kindness, affection and respect or obtain several contact numbers to be able to track the participant down in the future.

**Fig. 1 Fig1:**
[figure not shown]
Flow diagram of the progress through the phases of the randomized controlled trial

### Sample size

Based on previous studies of indicated prevention of depression in caregivers [10, 11, unpublished paper of Note 1] and studies that have administered therapies for depression by phone (see [13]), we estimate that a sample size of 56 participants per group (168 in total) will be sufficient to detect a difference of 19 % in the rates of incidence of depression episodes between experimental and control conditions, assuming α = .05 and a power (1 - β) of .80. However, assuming an attrition rate of 5-8 %, we estimate that the sample size for each of the groups should be approximately 60 subjects (180 in total).

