Moreover, the most effective interventions to reduce depressive symptoms and prevent depression are multicomponent cognitive-behavioral programs [8, 16]. Specifically, in an indicated prevention intervention, Vázquez and colleagues [11] applied cognitive techniques to change thought patterns (e.g., double-standard technique, priming) and behavioral techniques to active behaviors (e.g., pleasant activities planning, reinforcement). They found a significant reduction in the incidence of depression (1.1 % vs. 12.2 %) and depressive symptoms (Cohen's *d* = 1.05) when compared to the control group. Using a dismantling strategy could help identify the contribution of behavioral activation techniques to the therapeutic change. As a result, this can contribute to the improvement of the prevention program and to greater efficiency. The behavioral activation techniques should play an essential role because assuming the caregiver role entails a number of behavioral changes related to leisure and recreation, family life and work that may involve a loss of positive reinforcement and an increase in aversive experiences, factors relevant to the development of depression [17]. In fact, a link between the shortage of leisure activities for caregivers and depressive symptoms has been previously demonstrated [18]. Furthermore, previous research [19–22] comparing antidepressant medication, cognitive techniques aimed at the automatic thoughts and underlying schemes, and behavioral activation techniques have shown that behavioral interventions are sufficient to effectively and efficiently treat depression.

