## Discussion

In this study we will evaluate the efficacy of a brief cognitive-behavioral intervention of indicated prevention of depression and one consisting solely of behavioral activation techniques, both of them administered in a conference call to caregivers. The prevention programs applied in this study were adapted from a previous study by Vázquez and colleagues [11]. Based on their results, we expect to find a significant reduction in the incidence of depression and depressive symptoms in both intervention groups when compared to a usual care control group.

The use of a conference call to administer psychological interventions as an alternative to traditional face-to-face programs will increase the accessibility to mental health services and increase the tools available to professionals to reach a larger number of people, following the recommendations of National Institute of Mental Health Psychosocial Intervention Development Workgroup [40] and the New Freedom Commission on Mental Health [41]. The advantages of interventions delivered through via phone include anonymity, lower cost and increases in accessibility [42]. Similarly to depression therapies administered over the phone [13], we expect both interventions to significantly reduce depressive symptoms of the caregivers and prevent the emergence of new depressive episodes.

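### The stated 80% power is for a 19-point difference in incidence, but the only incidences the protocol reports differ by 11.1 points, and at those rates power is about 66–69% before dropout

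*Protocol article*

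**What the plan says.** The Sample size section puts the requirement at 56 per group, or 168 overall. Its claim for that number is that it "will be sufficient to detect a difference of 19 % in the rates of incidence of depression episodes between experimental and control conditions". The α is .05 and the power .80. The number is then inflated for attrition of 5–8% to about 60 per group. The sources named are several: "Based on previous studies of indicated prevention of depression in caregivers [10, 11, unpublished paper of Note 1"], together with telephone-therapy trials in depression. The section states no incidence for either arm, no time point and no test.

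Background: the face-to-face caregiver trial cited there as reference 11, also one of the sources above, is said to have shown "a significant reduction in the incidence of depression (1.1 % vs. 12.2" %), intervention against control. No time window is attached. These are the only intervention-versus-control incidences in the article.

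Discussion: both programs are adapted from that same trial. The authors write: "Based on their results, we expect to find a significant reduction in the incidence of depression and depressive symptoms in both intervention groups".

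Statistical analyses section: the analysis is by intention to treat, participants who drop out are scored as having had a major depressive episode, and cumulative incidence is compared between groups. The central hypothesis in the Background is that each of the two interventions beats control.

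**The concern.** The difference used for sizing (19 points) is larger than the whole control incidence in the one study whose rates the article prints (12.2%). The Discussion names that study as the ground for expecting a preventive effect. A reader who takes the 80% at face value will think each active-versus-control comparison is well powered for the effect already seen with the parent program. If the true rates are near those printed, it is not, and a null result on the primary outcome could be misread as lack of efficacy. The rule that scores dropouts as episodes adds the same proportion of non-informative events to each arm when dropout is equal. That shrinks the difference and raises the variance, and the inflation from 56 to 60 does not allow for it.

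**Working it through.** **Inputs.** From Sample size: 56 per group, 19-point difference, α = 0.05, power 0.80, attrition 5–8%. From Background: 1.1% vs 12.2%. From Statistical analyses: dropouts count as episodes. Assumptions: two-sided test (sidedness is not stated), pairwise 1:1 comparison of each intervention with control, equal dropout across arms.

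**Formulas.** With d = p₁ − p₂ and p̄ = (p₁ + p₂)/2:
- n = [1.96·√(2p̄(1−p̄)) + 0.8416·√(p₁(1−p₁) + p₂(1−p₂))]² / d²
- power = Φ{[d·√n − 1.96·√(2p̄(1−p̄))] / √(p₁(1−p₁) + p₂(1−p₂))}

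**1. The plan's own figure.** It cannot be reproduced from stated inputs, because no base rate is given. Leaving the base rate free, 25% vs 6% gives n = [1.96 × 0.5118 + 0.8416 × 0.4939]² / 0.19² = 2.013 / 0.0361 = 55.8, so 56 per group with 80.2% power. With a continuity correction, 22% vs 3% gives 56.4. The stated 56 therefore implies a control incidence of about 22–25%. Attrition: 56/0.95 = 58.9 and 56/0.92 = 60.9, which agrees with about 60.

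**2. Ceiling.** From a control incidence of 12.2%, the largest possible absolute reduction is 12.2 points. The reported one is 12.2 − 1.1 = 11.1 points.

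**3. Power at the reported rates.** p̄ = 0.0665, √(2p̄(1−p̄)) = 0.3524, √(p₁(1−p₁) + p₂(1−p₂)) = 0.3435.
- n = 56: (0.111 × 7.483 − 0.6906)/0.3435 = 0.408, power 65.8%
- n = 60: (0.111 × 7.746 − 0.6906)/0.3435 = 0.493, power 68.9%
- Exact enumeration of the uncorrected chi-square test: 71.7% and 75.2%
- For 80%: n = (0.6906 + 0.2891)² / 0.111² = 77.9, so 78 per group

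**4. Dropouts scored as episodes.** Each rate becomes p(1−δ) + δ. Power is by the formula above, at 60 per group.

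| Scenario | Dropout δ | Rates | Difference | Power |
|---|---|---|---|---|
| 1.1% vs 12.2% | 0 | 1.1% vs 12.2% | 11.1 | 69% |
| 1.1% vs 12.2% | 5% | 6.0% vs 16.6% | 10.5 | 44% |
| 1.1% vs 12.2% | 8% | 9.0% vs 19.2% | 10.2 | 36% |
| 6% vs 25% | 5% | 10.7% vs 28.8% | 18.1 | 70% |
| 6% vs 25% | 8% | 13.5% vs 31.0% | 17.5 | 64% |

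**5. Sensitivity to the unstated time window.** Keep the reported relative risk, 1.1/12.2 = 0.090, and vary the 12-month control incidence, before dropout:
- 15% vs 1.35%: power 76% at 56 per group, 79% at 60
- 20% vs 1.80%: power 88% at 56 per group, 90% at 60
- A 19-point difference needs a control incidence of 0.19/(1 − 0.090) = 20.9%

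**The case against.** Four points can fairly be made on the other side.

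- **Several sources.** The 19 points are nowhere attributed to the trial with 1.1% vs 12.2%. The section also cites another caregiver trial, an unpublished paper and telephone-therapy studies, whose rates the article does not show. This stands. A reader might infer that the sample size was derived from that one trial and contradicts it; the text does not support that. What it does show is that the only printed rates, from the trial on which the Discussion rests its expectation, do not support the 19 points.
- **Time window.** The 12.2% carries no follow-up period, and this trial counts cumulative incidence to 12 months. This also stands, and the result is sensitive to it, as step 5 shows. The ceiling in step 2 applies only if 12.2% is the right control rate for this trial's horizon.
- **Sound arithmetic.** A reader might call 56 a miscalculation. It is not: it is correct for 6% vs 25%, and the attrition step checks. The section also already words 19 points as a difference to detect, not as the expected effect. Merely leaving out arm-level rates would be ordinary condensation in an article.
- **Choice of test.** No test is named for comparing incidence. Fisher's exact test would give 51% at 56 per group and 57% at 60, but it would also put 6% vs 25% at only 74% with 56, so it is one scenario and not the headline. One-sided power at the reported rates is 77% and 79%.

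Pooling both active arms against control (112 vs 56) would give 82.8% at the reported rates, but the central hypothesis concerns each intervention. With 5–8% dropouts as episodes, pooled power at 120 vs 60 is 61–50%.

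**Conclusion.** The point holds in a limited form. The 80% figure is right for about 6% vs 25%, but the article's own incidences do not support it. At 1.1% vs 12.2%, pairwise two-sided power is about 66% at 56 per group and 69% at 60 (exact chi-square 72% and 75%). Once dropouts are scored as episodes, at 5–8% in every arm, power at 60 per group falls to about 44–36%. That rule also takes the favourable 6% vs 25% scenario below 80%, to about 70–64%.

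These figures assume a two-sided test, pairwise comparison, equal dropout across arms, and that the printed rates apply over this trial's follow-up. The stronger conclusion, that the trial is underpowered, does not follow: at the same relative risk, a 12-month control incidence near 20% would give about 88–90% before dropout, and the documents do not exclude that. What is established is that the stated power for the primary outcome depends on a control incidence about twice the only one reported, and on dropouts not being handled as the analysis section says they will be.

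**What to change.** Restate the Sample size paragraph with the assumed cumulative incidence in each arm, the source of each figure, the time point (12 months, if that is the one meant) and the test. Next to the 19-point scenario, report power at 60 per arm for 1.1% vs 12.2%. Give both scenarios with and without dropouts counted as episodes. If the other cited sources support a control incidence of about 22–25%, quote their rates and follow-up times there.

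The cost is one rewritten paragraph and a less favourable stated power. No extra enrolment and no change to design or analysis is asked for.

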### Participants, recruitment and eligibility criteria

Participants will be recruited from the Official Register of Caregivers of the Ministry of Labor and Welfare of the Galicia Regional Government in northwestern Spain. A random sample of caregivers stratified by area type [rural (<2000 inhabitants) or urban (≥2000 inhabitants)] and province (Coruña, Lugo, Pontevedra or Orense) will be selected. Previously we have determined that approximately 39 % and 44 % of caregivers have elevated depressive symptoms [10, 11] and 8.9 % have depressive episodes [5]. As a result, to achieve the estimated sample size of approximately 180 participants we will need to randomly select approximately 550 caregivers for a screening prior to the verification of the eligibility criteria.

Caregivers will be contacted by mail and invited to participate in the study. They will be asked to return a stamped postcard if they do not want to be contacted further. Caregivers who do not return that card will be contacted with a brief description of the study. Those who are interested will undergo a screening to assess depressive symptoms and history of depressive episodes. Those who meet the initial selection criteria will be invited to participate in a longer evaluation that will evaluate the inclusion and exclusion criteria.

To be enrolled in the study, participants must meet the following inclusion criteria: (a) be officially recognized by the authorities as caregivers for a relative in a situation of dependency, (b) have a telephone, (c) obtain a pretreatment score ≥ 16 in the Center for Epidemiologic Studies Depression Scale (CES-D [25]), (d) not meet the DSM-IV criteria for a major depressive episode [26], (e) not have a history of major depression, (f) give informed consent. We will exclude those subjects that at the time of the assessment: (a) have been receiving psychological or pharmacological treatment for the last two months, (b) experience other conditions that could act as confounders in the study (e.g., symptoms due to the direct physiological effects of a substance or a medical condition), (c) have medical and mental disorders of such severity that they require immediate intervention (e.g., suicidal ideation) or that would make it impossible to participate in the study (e.g., severe hearing impairment), (d) care for a family member that has a terminal diagnosis, (e) are planning to institutionalize the family member or to move.

### Randomization

Those subjects who meet the eligibility criteria and have signed the informed consent forms will be randomly assigned to the CBC, BAC or CG groups by an external statistician using a table of random numbers. The scrambling sequence will be communicated to researchers through numbered sealed envelopes, one for each participant, with instructions to use them in numerical order.

### Interventions

The manuals for the intervention protocols will be developed during the first months of the project. Psychologists who have been trained by two experienced clinicians, each with over 20 years experience in cognitive-behavioral therapies, will administer the interventions. Therapists will receive about 35 h of training consisting of theoretical and practical seminars and role-playing exercises. They will administer the interventions following the treatment manuals and will be monitored weekly. Each intervention will be administered via conference call and will consist of five 90-min group sessions once a week. All sessions will be recorded and the clinicians involved in the training of therapists will use the recordings to assess adherence to established protocols.

#### Cognitive-Behavioral Intervention via Conference Call (CBC)

CBC is an intervention based on the multifactorial integrative model of depression by Lewinsohn and colleagues [17], which considers depression as the outcome of behavioral, cognitive and emotional changes initiated by the environment and moderated by cognitive factors. The intervention will be adapted from a previous intervention of indicated prevention of depression applied face-to-face in a group format [11]. During the intervention the participants will be trained in various cognitive and behavioral skills such as self-monitoring of mood and activity, relaxation techniques, self-reinforcement, increasing pleasant activities, behavioral contracts, techniques aimed at increasing positive thoughts and decreasing depressogenic ones, training in assertive communication and strategies to increase social contacts.

#### Behavioral Activation Intervention via Conference Call (BAC)

BAC will also be adapted from the program developed by Vázquez and colleagues [11]. However, the intervention will focus on the behavioral activation component of the intervention. During the intervention the participants will be trained in different behavioral strategies such as self-monitoring of mood and activity, self-reinforcement, increasing pleasant activities, behavioral contracts, and training in assertive communication and in strategies to increase social interactions.

#### Usual Care Control Group (CG)

Usual care will constitute the control condition. People assigned to this group will receive no intervention or psychoeducational material. However, we will offer them the possibility of accessing any medical or psychological treatment (public or private) available in their community to treat depressive symptoms.

### Outcomes

Throughout the study, we will collect information on sociodemographic characteristics and situation of care, major depressive episode and other mental disorders, depressive symptoms, the mediating variables (negative thoughts, self-efficacy, reinforcement, social contacts), adherence to treatment, dropouts and satisfaction with the interventions (see Table 1). The self-administered instruments will be mailed to participants to complete them in their homes. The hetero-administered ones will be administered via telephone by trained evaluators who are unfamiliar with the purpose of the study, the interventions that will be administered and the random assignments into each group. Training of the evaluators will consist of 15 h of theoretical and practical workshops and role-playing on the instruments of measurement and evaluation strategies by one of the study investigators who has over 20 years experience in evaluation.

**Table 1 Tab1:** Overview of measures

Instrument	Intervention phase	Format
Participant characteristics		
Socio-demographic and care situation characteristics	Pre-treatment	Self-administered
Primary outcome		
Major depression: SCID-CV	Pre-treatment, Post-treatment, 1-, 3-, 6- and 12-month follow-ups	Hetero-administered
Secondary outcomes		
Depressive symptoms: CES-D	Pre-treatment, Post-treatment, 1-, 3-, 6- and 12-month follow-ups	Self-administered
Automatic negative thoughts: ATQ-N	Pre-treatment, Post-treatment	Self-administered
Reinforcement: EROS	Pre-treatment, Post-treatment	Self-administered
Register of social networking	Pre-treatment, Post-treatment	Self-administered
Self-efficacy: GSES	Pre-treatment, Post-treatment	Self-administered
Dropout and treatment adherence	During the intervention, Post-treatment, 1-, 3-, 6- and 12-month follow-ups	Hetero-administered
Satisfaction with the service received: CSQ-8	Post-treatment	Self-administered

*Note*: *SCID-VC* Structured Clinical Interview for DSM-IV Axis I Disorders, Clinician Version, *CES-D* Center for Epidemiologic Studies Depression Scale, *ATQ-N* Automatic Thoughts Questionnaire, *EROS* Environmental Reward Observation Scale, *GSES* General Self-Efficacy Scale, *CSQ-8* Client Satisfaction Questionnaire

#### Socio-demographic and care situation characteristics

Through the Characteristics and Status of Caregiver Questionnaire used in previous studies [10, 11] the following information will be collected: sex, age, marital status, social class, level of education, main occupation, relative cared for, gender and age of the person receiving care, duration (in years) of care and daily hours dedicated to care.

#### Primary outcome measure: major depression

Major depression will be diagnosed with the help of the Structured Clinical Interview for DSM-IV Axis I Disorders, Clinician Version (SCID-CV) [27]. This is a semi-structured interview providing DSM-IV diagnostics and consists of six modules (mood episodes, psychotic symptoms, psychotic disorders, mood disorders, substance use disorders, anxiety disorders, and other disorders). In the initial assessment we will use the entire interview, whereas only the major depressive episode module will be used in the subsequent assessments. The SCID-CV has good test-retest reliability and adequate reliability for psychiatric patients (kappa index = 0.61).

#### Secondary outcome measures

##### Depressive symptoms

We will evaluate the severity of the depressive symptoms using the self-reported scale CES-D [25] (Spanish version of Vázquez and colleagues [28]). This scale consists of 20 items in which the person reports how often they experienced each symptom in the last week by a Likert scale with 4 response options ranging from 0 (rarely or none of the time) to 3 (most of the time). The total score ranges from 0 to 60 and higher scores correspond to greater depressive symptomatology. Its internal consistency ranges from .85 to .90, with the Spanish version having a score of .89.

##### Automatic negative thoughts

The occurrence of automatic negative thoughts will be evaluated with the Automatic Thoughts Questionnaire (ATQ-N) [29], which has been translated into Spanish by following the guidelines of Guillemin and colleagues (using the translation / back-translation method) [30]. This questionnaire consists of 30 items in which the participant must indicate the frequency with which they experienced the thoughts during the last week on a Likert scale ranging from 1 (never) to 5 (always). The score ranges between 30 and 150 with a higher score indicating more negative thoughts. The internal consistency for the ATQ-N is .96.

##### Reinforcement

We will use the self-administered Environmental Reward Observation Scale (EROS) [31] (Spanish version of Barraca and Pérez-Álvarez [32]) to assess reinforcement. It has 10 items in which the participant evaluates the degree of positive reinforcement received contingently from the subject’s environment on a Likert scale ranging from 1 (strongly disagree) to 4 (strongly agree). The total score ranges from 10 to 40, with a higher score indicating a higher degree of positive reinforcement. The internal consistency of the Spanish version is .86.

